## Aims and objectives

The aims of the RECOLLECT Programme are to establish the effectiveness and cost-effectiveness of Recovery Colleges in England, and to identify how Recovery Colleges can be optimised to maximise the benefit for people with mental health problems.

Specific objectives, with the abbreviations used hereafter in brackets, are:To describe Recovery Colleges in England (Characterise)To establish Recovery College costs (Costs)To investigate changes over time in service user student outcomes for an inception cohort across multiple Recovery Colleges (Student outcomes)To investigate the relationships between fidelity, mechanisms of action and outcomes for an inception cohort (Fidelity, mechanisms and outcome)To assess the effectiveness of Recovery Colleges for an inception cohort (Effectiveness)To assess the cost effectiveness of Recovery Colleges for an inception cohort (Cost-effectiveness)To explore the relationship between Recovery College use and routine clinical NHS data (Clinical data) for a retrospective cohortTo establish the key contextual and organisational factors influencing fidelity and variation in outcomes (Organisational)To finalise the RECOLLECT multilevel change model (Change model)To use findings to maximise Recovery College effectiveness and coverage (Knowledge mobilisation).

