#### Measures

The RECOLLECT Fidelity Measure is a 12-item Recovery College manager-rated assessment [33]. It comprises seven non-modifiable components (Valuing equality; Learning; Tailored to the student; Co-production of the Recovery College; Social connectedness; Community focus; and Commitment to recovery) and five modifiable components (Available to all; Location; Distinctiveness of course content; Strengths-based; and Progressive). Each non-modifiable component is scored on a three-point scale from 0 (low fidelity) to 2. Each modifiable component is rated as either Type 1 or Type 2 (e.g. eligibility restricted to those affiliated with the host organisation, vs available to all), and as each modifiable component is independent, Recovery Colleges can score Type 1 on some components and Type 2 on others. No summary score is produced, since the relationship between fidelity and outcome is not empirically established.

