### Work package 2: Prospective pre-post study exploring Recovery College impact on student mental health outcomes

Work package 2 will address Objectives 3 (Student outcomes), 4 (Fidelity, mechanisms and outcomes) and 9 (change model).

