#### Sample

To address Objective 3 we have conservatively assumed a small but clinically significant within-person effect size of 0.2 [41]. With standard deviation (SD) of 5 based on the mean difference of total score of the primary outcome measure, the Manchester Short Assessment (MANSA) [42] between baseline and follow up at 12 months with 95% power and 5% significance, assuming an intra-class correlation coefficient (ICC) of 0.02 [43, 44], an individual autocorrelation of MANSA score over time of 0.5 [45] and within-cluster standard deviation (SD) of 5, we require a sample size of 500. With an estimate of 20% attrition rate by 12 months, we will recruit 625 participants, for an analysable sample of 500. We will recruit 625 newly registering students (25 per college) who currently use secondary mental health services. Exclusion criteria will be insufficient knowledge of English to complete the outcome measures.

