#### Analysis

To address Objective 3 (Student outcomes), we will compare primary outcome (total MANSA score) at baseline, 4, 8, and 12 months follow-up adjusted for baseline total MANSA score and accounting for hierarchical clustering of students at the level of Recovery College. The model will include the MANSA score as the outcome variable, baseline MANSA score and socio-demographic characteristics as explanatory variables at each time point. Specifically, we will fit a three-level random intercept linear regression model, considering observations from baseline, 4, 8 and 12 months at level 1, individuals at level 2 and Recovery Colleges at level 3. Secondary outcomes will be assessed similarly to the primary outcomes, using generalized linear mixed models (logistic, linear and Poisson depending on the distribution of our outcome variable).

The relationship between Fidelity Measure scores at the Recovery College level with primary and secondary outcomes will also be assessed using generalised linear mixed models. Where significant associations emerge, theoretical mechanisms of action will be added to models to examine potential mediating effects.

If indicated, we will refine the RECOLLECT multilevel change model by removing outcomes where there is no evidence of change at any time point.

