### Work package 5: Organisational case studies of Recovery Colleges

Work Package 5 addresses Objectives 8 (Organisational) and 9 (Change model).

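### Work Package 2 examines mediation only after a significant fidelity–outcome association, so real mechanisms under Objective 4 can go unexamined

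*Protocol article*

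**What the plan says.** Work Package 2 is assigned Objectives 3, 4 and 9. Objective 4 covers the relationships between fidelity, mechanisms of action and outcomes. The Analysis section first relates Fidelity Measure scores, at college level, to the outcomes in generalised linear mixed models. It then sets the condition for the mechanism step: "Where significant associations emerge, theoretical mechanisms of action will be added to models to examine potential mediating effects".

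On the fidelity scores, the Measures section of Work Package 1 describes seven components scored 0 to 2 and five classed as Type 1 or Type 2, and adds: "No summary score is produced, since the relationship between fidelity and outcome is not empirically established".

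The same Analysis section ends with a rule for the model itself, to be applied only if indicated, which refines it by "removing outcomes where there is no evidence of change at any time point".

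The only sample size calculation for Work Package 2 concerns change in the MANSA (Objective 3), where "we have conservatively assumed a small but clinically significant within-person effect size of 0.2". The article gives no power for the fidelity associations or for mediation.

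**The concern.** The order of the steps is the problem. The total association between fidelity and outcome has to reach significance before any mechanism enters a model. A total association is the sum of direct and indirect paths. It can be small or non-significant when an indirect path is real, either because paths of opposite sign offset each other or because the college-level test of the total is imprecise. Testing the total first is therefore not a valid screen for whether mediation exists.

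The screen also works with few units. Fidelity varies only between colleges, there are 25 of them, and the planning ICC says that colleges differ little. The mechanism part of Objective 4 could go unexamined because the gate stayed shut, not because the mechanisms were studied and found wanting. Conversely, with several components tested, the gate can open by chance.

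The removal rule raises a related but smaller worry. Lack of evidence of change becomes a ground for deleting an outcome, in a design with no control group, where change is not by itself a Recovery College effect and absence of change is not by itself absence of one.

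**Working it through.** **Inputs.** Work Package 2, Design and Sample: 25 colleges; 500 analysable students, so 20 per college; ICC 0.02; autocorrelation 0.5; effect size 0.2; 95% power; 5% significance (taken as two-sided); 20% attrition. Fidelity Measure: 12 components; test–retest reliability 0.60 for the measure (Background). Follow-up at 4, 8 and 12 months.

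**The plan's own figure.** With autocorrelation 0.5 the variance of a change is 2(1 − 0.5) = 1 times the score variance, so the SD of change equals the SD. Without clustering, n = ((1.960 + 1.645)/0.2)² = 325. The design effect is 1 + 19 × 0.02 = 1.38, giving 325 × 1.38 = 448 by normal approximation. A t test on 24 df with 25 × 20 students gives 95.5% power at 500 and 94.8% at 475, so 500 is the smallest 25 × m design that reaches 95%. Then 500/0.8 = 625. The stated numbers reproduce and are not at fault.

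**Power of the gate.** Suppose one component explains half of the true between-college variance. Take total variance as 1, so the student-level part is 0.98. The reliability of a college mean is 0.02/(0.02 + 0.98f/20), where f is the fraction of student-level variance left after averaging and adjustment. The correlation with the observed means is r = √(0.5 × reliability). Power uses Fisher's z: atanh(r) × √22, compared with 1.96.

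| Model | f | Reliability | r | Power |
|---|---|---|---|---|
| One visit, unadjusted | 1 | 0.29 | 0.38 | 47% |
| One visit, baseline-adjusted | 1 − 0.5² = 0.75 | 0.35 | 0.42 | 56% |
| Three visits, baseline-adjusted | (1 + 2 × 0.5)/3 − 0.5² = 0.417 | 0.49 | 0.50 | 73% |

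The adjusted rows assume autocorrelation 0.5 between every pair of visits and a college variance that baseline adjustment does not reduce. If the 0.60 reliability applied to a single component, r is multiplied by √0.60 = 0.775, and power falls to 30% in the first row and 48% in the last.

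A college-level regression with 23 df agrees for the unadjusted case: about 27%, 50% and 86% power if the component explains a quarter, half or all of the between-college variance.

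**Chance openings.** Twelve independent null components tested on the MANSA at 5%: 1 − 0.95¹² = 46% for at least one opening. With only the seven scored components: 1 − 0.95⁷ = 30%.

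**Removal rule, read as p > 0.05 at all three follow-ups.** The SE of a change is √(1.38/500) = 0.0525 SD, so the 95% CI half-width is 0.103 SD. With correlation 0.5 between the three tests, simulation compares this reading with removal only if all three intervals lie within ±0.2 SD:

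| True sustained change | Removed, p-value reading | Removed, interval rule |
|---|---|---|
| 0 | 87.5% | 84% |
| 0.05 SD | 68% | 63% |
| 0.1 SD | 27% | 23% |
| 0.2 SD | 0.2% | 0.2% |

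A 0.2 SD change present only at 12 months is removed 2.3% of the time under the p-value reading.

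**The case against.** The strongest defence is that the gate is less weak than a simple calculation suggests. The plan describes mixed models with baseline adjustment and repeated follow-ups for the outcomes. If the fidelity analysis uses the same structure, power in the half-variance case is 73%, not 47%. Oversampling at the seven Work Package 3 colleges (48 instead of 25 each) would add a little more. That stands, and it rules out saying that the gate mostly blocks real mechanisms. It does not repair the logic, because an indirect effect can exist without a significant total association at any power.

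Second, the number of tests is not fixed in the article. A reader might multiply 12 components by eight outcome scales to get 96 tests, with 4.8 false openings expected at 5%. The article does not say that each component is tested separately against each outcome, and five of the 12 are type classifications. Multiplicity handling may also sit in an analysis plan that is not shown. The chance-opening figures are therefore illustrations.

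Third, a reader might infer that Work Package 2 finalises the change model by significance, deleting true outcomes and keeping chance ones. The documents do not support this. The text says that the model will be refined, and only if indicated. It refers to evidence, not to a p-value. Work Package 5 shares Objective 9, its case studies explore the proposed mechanisms qualitatively, and finalisation is discussed there. A sustained change of 0.2 SD, the size that the plan calls clinically significant, would be removed only about 0.2% of the time even under the p-value reading.

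**Conclusion.** The point holds for the mediation gate. As written, mechanisms are modelled only after a significant fidelity–outcome association, which is neither necessary for mediation nor well powered with 25 colleges. For a component explaining half of the between-college variance, the chance of passing is about 47% to 73% depending on the model, and about 30% to 48% if a reliability of 0.60 applies to the component. These figures rest on an ICC of 0.02, 20 analysable students per college, autocorrelation 0.5 and a two-sided 5% test. Real mechanisms can go unexamined in the quantitative part of Objective 4, and some openings can be due to chance. An unseen analysis plan could define thresholds and multiplicity control, but it could not keep this gate and also estimate every hypothesised path.

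The removal rule is a secondary matter of interpretation. An interval-based rule has the better rationale but changes error rates little (27% against 23% removal at 0.1 SD), so this part does not carry the finding.

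**What to change.** Remove the significance condition. For every path pre-specified in the change model, estimate the fidelity-to-mechanism and mechanism-to-outcome paths and the multilevel indirect effect, with confidence intervals, whether or not the total association is significant. Label these analyses exploratory. Control the false discovery rate over the fidelity–outcome tests when reporting them, without using the result to decide which mechanisms are modelled.

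For refining the change model, report each outcome's estimated change and 95% CI at each visit against the plan's own 0.2 SD, and call an outcome inconclusive where the interval includes 0.2. State that change in an uncontrolled study does not by itself establish or exclude a Recovery College effect.

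The cost is a change of wording and modest extra analysis, with no new data. The downside is wide intervals for some paths, and some outcomes left as inconclusive.

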### Work package 3: Prospective controlled study exploring the effectiveness and cost effectiveness of Recovery Colleges

Work package 3 will address Objectives 5 (Effectiveness) and 6 (Cost-effectiveness).

#### Design and rationale

Work package 3 will employ a prospective controlled study design and include seven of the Recovery Colleges from Work Package 2, with which it will run in parallel. A non-randomised design will be employed due to the impossibility of individual level randomisation; most mental health service users have access to a Recovery College, even if not available in their Trust. The seven Recovery Colleges were selected for being linked to an NHS Trust which has access to a Clinical Record Interactive Search (CRIS) system, as this will be used to identify the control group.

#### Sample

Intervention group eligibility will be as for Work Package 2; eligible controls will not be attending a Recovery College at baseline, or have previously attended a Recovery College. Work Package 3 will require approximately 48 students at each of the seven Recovery Colleges to form an intervention group of 330 participants; and 660 participants in total with the control group. This sample size is needed for 90% power to detect an effect size of 0.2 on the MANSA [46] using a two-sided test for the difference between two independent means and assuming α = 0.05. To meet this recruitment target, students at the seven Recovery College sites for Work Package 3 will be oversampled (i.e. 48 instead of 25 per site) relative to the others in Work Package 2.

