#### Procedures

Work Package 3 will run alongside Work Package 2. At the seven Recovery College sites involved in Work Package 3, participants will be asked if they would like to take part in Work Package 3 by consenting to data linkage using CRIS. Those that consent will comprise the intervention group for Work Package 3. This is outlined in Fig. 4 below. To identify the control group, propensity score matching [58] will be employed using the CRIS system at each site. This is a statistical matching technique that attempts to create a comparable control group for the Recovery College intervention group by accounting for the covariates, such as demographics and clinical history, that predict outcomes. Reverse anonymisation will be undertaken by CRIS staff and potential control participants will be contacted by NHS Trust staff working with CRIS staff to find out if participants are interested in hearing more about the study. Those that are will be provided with information sheets and will need to give informed consent to take part. The intervention group will complete those measures used in Work Package 2 and listed above at the same time points of baseline, 4, 8 and 12 months. The control group will complete the primary outcome measure and a restricted set of those measures used in Work Package 2 and the Work Package 3 intervention group, to reduce burden. Participants in Work Packages 2 and 3 will be compensated for their time completing assessments.

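### In Work Package 3, 330 per group gives about 73% power, not 90%, for an effect size of 0.2 under the test the protocol names

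*Protocol article*

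**What the plan says.** The Sample section of Work Package 3 in the protocol article asks for "approximately 48 students at each of the seven Recovery Colleges to form an intervention group of 330 participants". Adding as many controls brings the planned total to 660. It then justifies the number: "This sample size is needed for 90% power to detect an effect size of 0.2 on the MANSA [46] using a two-sided test". The comparison it names is of means in two independent groups, with alpha at 0.05. It mentions no attrition, baseline correlation, repeated measurement or pairing.

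The Sample section of Work Package 2 does state such inputs for its own calculation: "With an estimate of 20% attrition rate by 12 months, we will recruit 625 participants", and "an individual autocorrelation of MANSA score over time of 0.5".

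The two studies share students. Under Work Package 3, Procedures, Work Package 2 participants at the seven sites are asked to agree to record linkage: "Those that consent will comprise the intervention group for Work Package 3". They are measured at baseline, 4, 8 and 12 months, as in Work Package 2.

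**The concern.** The Work Package 3 sentence gives every input of a standard two-sample calculation, so it can be checked without any other document. A difference of 0.2 SD with 90% power normally needs more than 500 per group, and 330 is well below that.

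This is the only power statement for Objective 5, the effectiveness question. Under the named test, the chance of missing a true 0.2 SD effect is about 27%, not the stated 10%. Anyone who relied on the stated 90% when interpreting a null result would put too much weight on it.

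**Working it through.** **Inputs from Work Package 3, Sample:** standardised difference d = 0.2 (SD = 1; read as standardised, as in Work Package 2); two-sided alpha 0.05, z = 1.960; power 90%, z = 1.2816; 330 per group.

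**Inputs borrowed from Work Package 2, Sample (assumptions for Work Package 3):** 20% attrition by 12 months; baseline-to-follow-up correlation r = 0.5.

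**1. Attempt to reproduce the stated size.** n per group = 2(1.960 + 1.2816)² / 0.2² = 525.4, so 526 per group and 1,052 in total (527 per group by the t distribution). The stated 330 is 330/526 = 63% of this. A one-sided test at 0.05 would need 429 per group, so sidedness does not explain the gap.

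**2. Power with 330 per group.** 0.2 × √(330/2) − 1.960 = 2.569 − 1.960 = 0.609, giving 72.9% (noncentral t: 72.8%). Using 7 × 48 = 336 per group gives 73.6% (t: 73.5%).

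**3. Detectable effect at 90% power.** 3.2415 × √(2/330) = 0.252 SD.

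**4. With 20% loss in both groups (assumption).** 330 × 0.8 = 264 per group. 0.2 × √(264/2) − 1.960 = 2.298 − 1.960 = 0.338, giving 63.2% (t: 63.1%). Detectable effect: 3.2415 × √(2/264) = 0.282 SD. To keep 526 per group after 20% loss would take 526/0.8 = 658 per group.

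**5. Credit for baseline adjustment at one time point.** The residual variance is multiplied by 1 − r². At r = 0.5 the factor is 0.75, so the effective d is 0.2/√0.75 = 0.231. Power by assumed r (normal approximation):

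| r | 330 per group | 264 per group |
|---|---|---|
| 0.3 | 76.8% | 67.3% |
| 0.5 | 84.3% | 75.6% (t: 75.4%) |
| 0.6 | 89.5% | 81.9% |
| 0.7 | 94.9% | 89.6% |
| 0.8 | 99.0% | 96.9% |

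The correlation needed for 90% is r = √(1 − n/525.4): √(1 − 330/525.4) = 0.61 and √(1 − 264/525.4) = 0.71. At r = 0.5 the detectable effects are 0.252 × √0.75 = 0.219 SD (330) and 0.282 × √0.75 = 0.244 SD (264).

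**6. Effect averaged over three follow-ups.** With equal correlations of 0.5 throughout, the variance factor is (1 + 2r)/3 − r² = 0.667 − 0.25 = 0.417. Power is then 97.8% (330) or 94.5% (264).

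**7. Possible origin of the figure (inference only).** 526/0.8 = 658 is close to 660, which would mean a per-group size was read as a total. The one-sample or paired formula gives 263, and 263/0.8 = 329 is close to 330. Neither is the named test.

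**The case against.** The strongest reply is that the planned analysis is not a bare two-sample test. Under Work Package 3, Analysis, the model adjusts for baseline MANSA, sociodemographic characteristics and the matching factors, and uses all three follow-ups. Real power may therefore be higher than 73%. At r = 0.5 and 330 per group the shortfall is 84% against 90%, and a higher correlation or an averaged effect would reach 90%. That stands as a statement about the model. It does not support the sentence in the Sample section, which names a different test and states neither a correlation nor averaging. The Analysis section compares groups at each follow-up, lets the effect differ by time point through an interaction, and refers to 12 months as the primary endpoint.

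It is also fair to say that 20% attrition and r = 0.5 are stated for Work Package 2 students only. Controls are recruited differently and complete fewer measures, and no attrition figure is given for them. The finding therefore rests on 73%; the 63% and 75% figures are conditional.

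A reader might infer several stronger points that the documents do not support:

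- **That 330 contains no allowance for loss, or presumes near-universal consent to linkage because 7 × 48 = 336.** The 48 is approximate, and 330/7 = 47.1 may simply have been rounded up. The origin routes in step 7 would include a 20% allowance. All that can be said is that none is stated.
- **That leaving out the Work Package 2 intra-class correlation of 0.02 lowers power further.** Controls are matched within each site and the model has a college intercept. If controls share the site level, a common college effect largely cancels. A between-college variance of the treatment effect is a different quantity, which the protocol neither states nor models.
- **That only an averaged effect could exceed 90%.** That holds at r = 0.5 with baseline as the sole covariate, not in general.

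**Conclusion.** The concern holds as an internal contradiction: sample size, power, effect size and named test cannot all be right. Under the test as written, 330 per group gives about 73% power for 0.2 SD and detects about 0.25 SD with 90% power; 90% power for 0.2 SD needs about 526 per group. This part needs no assumption beyond reading 0.2 as a standardised difference. The statistical analysis plan, which is not shown, cannot reconcile figures that the article itself gives in full.

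Two further figures are conditional. With 20% loss in both groups, power is about 63% and the detectable effect about 0.28 SD. With single-time-point baseline adjustment at r = 0.5, power is about 84% (330) or 75% (264). The documents do not show that the study is too small for its planned model; they show that the stated justification is wrong as written.

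**What to change.** Keep recruitment as it is and correct the power statement in Work Package 3, Sample, in one of two ways.

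1. Report what the named test delivers. For example: 330 per group gives about 73% power to detect 0.2 SD with a two-sided two-sample test at alpha 0.05, and 90% power to detect about 0.25 SD. Then add, marked as assumptions for the sponsor to confirm: with 20% attrition in both groups (264 per group), about 63% power and 0.28 SD; with baseline adjustment at one time point and a correlation of 0.5, about 84% (330) or 75% (264).
2. If 330 and 90% came from another calculation, such as a baseline-adjusted or averaged effect, state that test with its correlation, attrition and time point, and check that it gives 330 per group.

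Use the corrected figures when interpreting a null result. The cost is one paragraph and, under the first option, a less favourable stated power. No extra participants and no design change are needed.
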